### Work plan

An intervention schedule has been established, with a total duration of 6 months, which is divided into three blocks:

#### Block 1

This first block focuses on the selection of the target population according to inclusion criteria. Firstly, a group session to present the program and the methodology of the study will be carried out. During the first 15 days of the study, a focus group with professionals to reach a consensus on the intervention will be held. Subsequently, the appropriate modifications will be made to improve and adapt to the dietary and nutritional intervention.

Consequently, the recruitment and initial psychopathological and nutritional assessment of the participants will be carried out, using the PANSS (45) and PSP (46) scales. For the nutritional evaluation, the analytical and anthropometric basal determination of the participating patients will be carried out, as well as the evaluation of the habitual dietary pattern through a validated FFQ (47) and weekly record of the main dishes and foods consumed. Similarly, an estimate of the intestinal bacterial flora is required employing stool culture.

#### Block 2

The second block includes the implementation of the 6-month individual nutrition education program (associated with 2 months of educational reinforcement, according to block 3). It will consist of eight sessions, the first four being biweekly, followed by 4 monthly, to which four sessions of educational reinforcement will be added to the 3 and 5 months of study. The minimum duration of each session has been established for 30 min. However, this length could be different, considering the characteristics of the participants. The control group will be made up of those participants who will receive standardized dietary advice (35). In this sense, the education content in the intervention group will be based on general principles of conventional dietary advice in an intensified manner (36), centered on the acquisition of specific knowledge about: (I) Underlying mental pathology, lifestyles and associated comorbidities; (II) Immediate principles: Carbohydrates, lipids, proteins, fiber, vitamins, and minerals; energy needs; consumption requirements; (III) Water requirements; (IV) Foodstuff; (V) Description and justification of prescribed prebiotic and probiotic diet; (VI) Culinary techniques: conservation of properties of the prebiotic and probiotic diet; (VII) Optimal distribution and interchange of foods with high prebiotic and probiotic content; (VIII) Feeding in particular situations.

In both the IG and the CG, visual support resources will be used during the development of the established sessions.

#### Block 3

Finally, to evaluate the effectiveness of the intervention, the modification in the nutritional, the cardio-metabolic, and the psychopathological area will be assessed. For doing this, researchers will carry out anthropometric determination, clinical evaluation, the performance of stool culture, and the study of the dietary pattern, as we commented above.

Likewise, in this block, an educational reinforcement (both in IG and CG) of what was treated in Block 2 will be offered, 3 and 5 months after the beginning of the block, every 15 days for the IG and monthly for the CG.

Once the intervention is concluded, the analysis of the collected data will be performed, culminating in the development of the scientific production and the writing of the research report.

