## Methods/design

### Study aims

#### Main objective

Determination of the nutritional and cardio-metabolic efficacy of a prebiotic and probiotic dietary intervention in patients with schizophrenia spectrum disorders.

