## Discussion

Firstly, it is expected to obtain the necessary information for the determination of the optimal dietary pattern for those participants in the study, thus allowing the development of a nutritional intervention with high prebiotic and probiotic content, appropriate for the population under study.

Likewise, the aim is to ensure that all participants improve their health status through the adaptation of the feeding pattern, developing adherence to healthier lifestyles adapted to the conditions of each patient.

Finally, it is expected to demonstrate that an adequate dietary modulation with a high prebiotic and probiotic content, leads to a significant improvement in the nutritional status and, therefore, the cardio-metabolic, of the participants, mediated by the microbiota-intestine-brain axis. Furthermore, it is presumed to reach a degree of evidence that allows establishing nutritional management as an effective therapeutic intervention in the psychopathological treatment of patients with schizophrenia spectrum disorders, in any of its variants.

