### Limitations

Potential limitations lie in the sample size of subjects included during the recruitment phase, the possible loss or non-cooperation of participants, and the loss or non-cooperation of participants in the intervention phase (especially those subjects with a predominance of negative schizophrenia symptomatology). This fact can lead to a possible lack of representativeness of the target population. Thus, to reverse this situation, the recruitment of the target population will be increased (more than doubled).

Likewise, the lack of capacity to prescribe symbiotic formulas and placebo management by mental health nurses, according to the legislative context in which the study will be carried out, prevents us from knowing the accurate range that an intervention with a high symbiotic content could have on these patients. Nevertheless, it is essential to emphasize that the main objective of the intervention is to assess the efficacy of a strategy based on health education. This tool is very cost-effective and is available for nursing professionals. Furthermore, from our perspective, this intervention can significantly impact the lifestyle habits of these patients in a sphere that has been forgotten as part of the traditional treatments.

Finally, the available evidence on the object of study makes it difficult to contrast the results obtained in different contexts of application.

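### The arms differ in intensity, reinforcement and self-recording as well as in prebiotic/probiotic content, so the trial can support a conclusion about the whole education programme but not about that content or a microbiota pathway

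*Protocol article*

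**What the plan says.** All places are in the protocol article.

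- **Main objective.** "Determination of the nutritional and cardio-metabolic efficacy of a prebiotic and probiotic dietary intervention in patients with schizophrenia spectrum disorders".
- **Discussion.** "it is expected to demonstrate that an adequate dietary modulation with a high prebiotic and probiotic content, leads to a significant improvement" in nutritional and hence cardio-metabolic status. The improvement is described as "mediated by the microbiota-intestine-brain axis".
- **Limitations.** Synbiotic formulas and placebo cannot be prescribed by the nurses, and "the main objective of the intervention is to assess the efficacy of a strategy based on health education".
- **Study design and Work plan, Block 2.** The IG receives intensive individual guidance. According to Block 2, "the education content in the intervention group will be based on general principles of conventional dietary advice in an intensified manner". Eight IG topics are listed. The CG receives conventional or standardised advice, whose topics are not listed. Individual delivery and visual aids are common to both arms.
- **Work plan, Block 2 (schedule).** There are eight sessions of at least 30 minutes each, plus four reinforcement sessions. The text does not say whether the CG also has the eight.
- **Work plan, Block 3.** Reinforcement goes to both arms at 3 and 5 months, "every 15 days for the IG and monthly for the CG".
- **Abstract (Methods) and Study design.** IG participants complete a weekly record of prebiotic/probiotic foods throughout the 6 months, as a measure of adherence. Block 1 of the Work plan also lists a weekly food record in the baseline assessment, without limiting it to one arm.

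**The concern.** The expected conclusion names one ingredient of the programme and one biological pathway. Randomisation supports a causal statement about everything that differs by arm, taken together. If the IG also receives more intensive teaching, more frequent reinforcement and a self-monitoring task, a difference between arms could come from any of these or from the diet.

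The outcomes make this a practical matter. Weight, BMI, waist, blood pressure, lipids and social functioning could all plausibly respond to extra contact and food recording without any change in prebiotic or probiotic intake. A positive trial would then be reported as evidence for the content, or for a microbiota mechanism, when it shows only that the programme outperformed conventional advice. Blinding is a separate matter: perfectly blinded assessors would leave the explanations just as inseparable.

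**Working it through.** **1. What differs by arm**

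| Element | IG | CG | Status |
|---|---|---|---|
| Prebiotic/probiotic diet advice | yes | not described | intended contrast |
| Intensity of guidance | intensified | conventional | explicit (Study design; Block 2) |
| Reinforcement | every 15 days | monthly | explicit (Block 3) |
| Weekly record during the 6 months | yes | not stated | explicit for IG (Abstract; Study design) |
| Weekly record at baseline | yes | yes, as written | shared (Block 1) |
| General and lifestyle topics | listed | not itemised | difference not shown |
| Individual delivery, visual aids | yes | yes | shared |

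**2. Contact, by arithmetic**

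Reinforcement is read as two one-month periods, at 3 and 5 months. This reading is an assumption.

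- IG: 2 months × 2 per month = 4 sessions. This reproduces the four reinforcement sessions given in Block 2.
- CG: 2 months × 1 per month = 2 sessions. The ratio is 4/2 = 2.

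Total contact if the CG also attends the eight main sessions:

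- IG: 8 + 4 = 12 sessions, at least 12 × 30 = 360 min.
- CG: 8 + 2 = 10 sessions, at least 10 × 30 = 300 min.
- Ratio: 12/10 = 1.2.

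Because CG attendance is not stated, the total could differ by more. With an assumed 4 main CG sessions the ratio is 12/6 = 2.0. With an assumed single session it is 12/3 = 4.0.

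**3. Self-recording**

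6 × 52/12 = 26 weekly records in the IG, against none stated for the CG after baseline.

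**4. Can the analysis separate the components?**

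The Statistical analysis section says that multivariate tests will adjust for confounding by the independent variables. Those listed are sociodemographic, therapeutic and clinical. Intensity, reinforcement schedule and assignment of the record are fixed by arm, so once arm is in the model there is nothing left to estimate separately. The food frequency questionnaire and stool culture at baseline and 6 months can describe whether diet and flora changed. Any such change would itself follow from the whole package.

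**5. Illustration with assumed rates**

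Suppose that prebiotic/probiotic content has no effect and the other elements raise a response rate from p₁ to p₂. With n = 25 per arm, two-sided 5% and p̄ = (p₁ + p₂)/2:

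power = Φ{ [ (p₂ − p₁) − 1.96·√(2p̄(1 − p̄)/n) ] / √[ (p₁(1 − p₁) + p₂(1 − p₂))/n ] }

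- 0.10 to 0.40: (0.30 − 1.96 × 0.1225)/0.1149 = 0.52, so power is about 0.70.
- 0.30 to 0.60: (0.30 − 1.96 × 0.1407)/0.1342 = 0.18, so power is about 0.57.
- A 40-point rise from the same control rates gives about 0.89 and 0.83.

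The rates are not from the protocol. They show only that a significant result would not, by itself, point to the diet.

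**The case against.** The strongest reply is that this is a legitimate comparison of a package with conventional advice, and that the protocol says so. The Limitations section describes a health-education strategy. The Main objective speaks of a dietary intervention, which the Abstract and Study design describe as an individual education programme. Read that way, the two objectives describe the same thing, and a contradiction between them is not established. This stands: the Main objective needs clarifying and is not shown to be wrong. It does not cover the Discussion, which names the content as the cause and adds a mediating axis. The Limitations section concedes only that formulas and placebo are unavailable. It does not mention unequal intensity, reinforcement or recording.

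Several stronger readings are tempting but unsupported:

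- A reader might infer that the arms differ in lifestyle and general nutrition teaching, because five of the eight IG topics (I to IV and VIII) are not about prebiotics or probiotics. The CG syllabus is not itemised and the IG content builds on conventional advice, so much of this may be shared.
- A reader might infer that the IG has twice the contact. The 2:1 ratio applies to reinforcement only. Reinforcing Block 2 material in both arms suggests that the CG attends Block 2 sessions too, which gives 12 against 10.
- A reader might infer that the CG keeps no food record at all. The baseline assessment includes one. The 6-month IG record also logs prebiotic/probiotic foods, so it is tied to that component, though it may still act as self-monitoring.
- Saying that anywhere from 0 to 100% of an effect could be non-specific means only that the share is not identifiable. It does not measure the size of the problem.

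**Conclusion.** The point holds for what the trial may conclude. Three differences beyond dietary content are explicit: intensified guidance, reinforcement at about 4 against 2 sessions, and about 26 weekly records in the IG with none stated for the CG after baseline. Total contact may differ only modestly, at about 12 against 10 sessions. That figure assumes CG attendance at the eight main sessions and two one-month reinforcement periods. A difference in general or lifestyle topics remains possible but is not shown.

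The design supports a conclusion about the whole intensive programme against conventional advice. It does not support the Discussion's attribution to prebiotic/probiotic content or to microbiota mediation. The share of any effect due to content cannot be estimated from these two arms. None of this makes the randomised comparison itself invalid.

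**What to change.** Reword the Discussion, and clarify the Main objective, so that both match the Limitations section. The objective and conclusion should concern an intensive education programme oriented to prebiotic and probiotic foods, with content, contact and self-monitoring taken together, against conventional dietary advice. Neither should make a separate claim for prebiotic/probiotic content or for mediation by the microbiota. It would also help to state whether the CG attends the eight Block 2 sessions and to list the CG topics, so that readers can see what the contrast contains.

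This costs only wording. The downside is a less specific claim. If the sponsor wants to keep the content claim, contact, general topics and food recording would have to be the same in both arms. That would take nurse time and probably narrow the contrast between arms. It is a design choice on which reasonable statisticians would differ, and it is not needed for the programme-level conclusion.

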## Discussion

Firstly, it is expected to obtain the necessary information for the determination of the optimal dietary pattern for those participants in the study, thus allowing the development of a nutritional intervention with high prebiotic and probiotic content, appropriate for the population under study.

Likewise, the aim is to ensure that all participants improve their health status through the adaptation of the feeding pattern, developing adherence to healthier lifestyles adapted to the conditions of each patient.

Finally, it is expected to demonstrate that an adequate dietary modulation with a high prebiotic and probiotic content, leads to a significant improvement in the nutritional status and, therefore, the cardio-metabolic, of the participants, mediated by the microbiota-intestine-brain axis. Furthermore, it is presumed to reach a degree of evidence that allows establishing nutritional management as an effective therapeutic intervention in the psychopathological treatment of patients with schizophrenia spectrum disorders, in any of its variants.

### Limitations

Potential limitations lie in the sample size of subjects included during the recruitment phase, the possible loss or non-cooperation of participants, and the loss or non-cooperation of participants in the intervention phase (especially those subjects with a predominance of negative schizophrenia symptomatology). This fact can lead to a possible lack of representativeness of the target population. Thus, to reverse this situation, the recruitment of the target population will be increased (more than doubled).

Likewise, the lack of capacity to prescribe symbiotic formulas and placebo management by mental health nurses, according to the legislative context in which the study will be carried out, prevents us from knowing the accurate range that an intervention with a high symbiotic content could have on these patients. Nevertheless, it is essential to emphasize that the main objective of the intervention is to assess the efficacy of a strategy based on health education. This tool is very cost-effective and is available for nursing professionals. Furthermore, from our perspective, this intervention can significantly impact the lifestyle habits of these patients in a sphere that has been forgotten as part of the traditional treatments.

Finally, the available evidence on the object of study makes it difficult to contrast the results obtained in different contexts of application.

## Ethics statement

The study will be carried out respecting the fundamental principles established in the Declaration of Helsinki (1964)50, the Council of Europe Convention on Human Rights and Biomedicine (1997)51, the UNESCO Universal Declaration on the Human Genome and Human Rights (1997)52. The research will also follow the requirements established by Spanish legislation (Organic Law 3/2018 of 5 December and Law 41/2002 of 14 November). This study protocol has been registered on the platform clinicaltrials.gov (NCT04366401). This research also has the permission of the Zamora Health Area Drug Research Ethics Committee at the Regional Government of Castile and León, Spain (No. reg. 468). All the information analyzed by the principal investigator of this study is subject to the maintenance of professional secrecy. In any case, each participant will be assigned a code as a registry, where all the comparative data will be mechanised in an anonymous way, delimiting the access to the database only to the personnel linked to the development of the study, previous authorisation of the investigator in charge of it.
